### Statistical analysis

The study outcomes will be presented as mean, standard deviation (SD), median, minimum, and maximum for continuous data and as frequencies and proportions for categorical data. The changes within groups from the baseline to the outcome measurement periods, according to each outcome, will be assessed with paired *t*-test (or Wilcoxon's rank sum test if the data do not meet the normality assumption). Between-group changes at each time point will be assessed by a two-sample *t*-test (or a Wilcoxon rank sum test will be used if normality is not met). Repeated measures analysis of covariance (ANCOVA) will assess group differences across time points, using baseline as a covariate. In addition, subgroup analyses will be conducted by age (19–64 and 65+).

For categorical variables, Pearson's chi-square test (or Fisher's exact test if the number of cells with an expected frequency of < 5 exceeds 20%) will be applied, and McNemar's test will analyze intra-group comparisons. In the case of physical examination, the results at each time point will be categorized as Normal, Abnormal Not Clinically Significant, and Abnormal Clinically Significant and the frequencies will be reported. For the concomitant medications, the number of participants who were taking concomitant medications, the percentage, and the number of doses will be reported.

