### Primary outcomes

#### Functional Oral intake Scale (FOIS)

The FOIS scale will be assessed as a primary outcome during the baseline and post-intervention periods. FOIS is a reliable and valid ordinal scale widely used for clinical and research purposes to assess changes in functional oral intake of food and liquids in patients with oropharyngeal dysphagia. FOIS is sensitive to changes in oral intake of food and liquid over time in stroke patients. This characteristic is essential when documenting overall stroke recovery or for detailed improvement associated with rehabilitation efforts. The scale ranges from level 1 (nothing by mouth) to level 7 (a full unrestricted oral diet) (31, 32).

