#### Penetration-aspiration Scale (PAS)

As a primary outcome, PAS will be assessed at Baseline and Post-intervention. The PAS is a standard scale to assess clinical practice and research deglutition. It is composed of an 8-point scale used to characterize the location of airway invasion events and the patient's response during videofluoroscopic swallowing studies. The scale was designed to capture three constructs: depth of airway invasion, material remaining after swallowing, and patient's response to aspiration. The scale ranges from score 1 (Material does not enter the airway) to score 8 (Material enters the airway, passes below the level of the vocal folds, and no effort is made to eject) (33, 34).

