### Sample size estimates

Due to the feasibility nature of the study, the primary goal is to evaluate the safety, practicability, and preliminary effects of optimized tDCS stimulations with personalized electrode placement in patients with post-stroke dysphagia. Consistent with established guidelines for feasibility and pilot studies, a formal power calculation for efficacy was not performed. Instead, the sample size of 30 participants (15 per group) was determined based on practical considerations and precedent from previous studies in this field. Specifically, a similar previous study (16) demonstrated protocol feasibility and observed clinically relevant improvements in swallowing function among 28 participants (14 per group) undergoing a 20-session tDCS intervention. Our study adopts a comparable intervention schedule and aims to provide reliable estimates of key feasibility outcomes-including recruitment rates, adherence, and adverse event profiles-while also generating preliminary data on the variability and potential effect size of our primary and secondary outcome measures. These findings will be essential for informing the design and sample size calculation of a future, large-scale randomized controlled trial.

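### The fallback named for within-group change is the Wilcoxon rank-sum test, which ignores the pairing; the signed-rank test is needed there

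*Protocol article*

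**What the plan says.** The Statistical analysis section of the protocol article sets out three relevant comparisons.

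- **Within-group, scale outcomes:** "The changes within groups from the baseline to the outcome measurement periods, according to each outcome, will be assessed with paired" *t*-test, with the alternative "Wilcoxon's rank sum test if the data do not meet the normality assumption".
- **Between-group, scale outcomes:** a two-sample *t*-test, "or a Wilcoxon rank sum test will be used if normality is not met".
- **Within-group, categorical outcomes:** "McNemar's test will analyze intra-group comparisons".

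The signed-rank test is not named anywhere in the article. Under Sample size estimates, "the sample size of 30 participants (15 per group) was determined based on practical considerations and precedent". The two primary outcomes are short ordinal scales: FOIS runs from level 1 to level 7, and for PAS, "It is composed of an 8-point scale used to characterize the location of airway invasion events".

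**The concern.** The same independent-samples test is named as the fallback for both a paired and an unpaired comparison. It suits the unpaired one. For the paired one it treats 15 baseline scores and 15 later scores as if they came from 30 different people, and so discards the information that each participant is their own control.

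The fallback is likely to be used. Change scores on a 7- or 8-level scale in 15 people are coarse and heavily tied, so a normality check may well fail for the two primary outcomes. At stake is the reported significance of change within each arm. These tests would understate change in both arms, in a trial meant to supply preliminary evidence for a larger one.

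**Working it through.** The plan states no power, alpha or p-value for this analysis, so there is no figure of its own to reproduce.

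**Inputs from the article:** 15 participants per group; FOIS with 7 levels; PAS with 8 levels.

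**Assumptions, not in the article:** two-sided 5% level; SD 1.5 levels; a mean gain of one level; baseline-to-later correlation *r* from 0.3 to 0.8.

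**Step 1: why the p-values are too large.** Take the simpler case of a difference in means.

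- Standard error if the samples were independent: SD × √(2/n) = 1.5 × √(2/15) = 0.548.
- Standard error for paired data: SD × √(2(1 − r)/n). This is the first value times √(1 − r).
- At r = 0.3: 0.548 × 0.837 = 0.458. A one-level gain is 1/0.458 = 2.18 standard errors.
- At r = 0.7: 0.548 × 0.548 = 0.300. A one-level gain is 1/0.300 = 3.33 standard errors.
- An independent-samples test scores the gain as 1/0.548 = 1.83 standard errors whatever *r* is.

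The loss therefore grows with the correlation.

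**Step 2: simulation of the rank tests.** Correlated normal scores were rounded and clipped to 1–7, with 15 pairs. Both tests were applied to the same pairs. Values are approximate.

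| Correlation | Rank-sum, no change | Rank-sum power, one-level gain | Signed-rank power, one-level gain |
|---|---|---|---|
| 0.3 | 2.4% | 38% | 49% |
| 0.5 | 0.9% | 36% | 62% |
| 0.7 | 0.2% | 35% | 80% |
| 0.8 | 0.1% or less | 33% | 92% |

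Under no change the signed-rank test rejects about 4% to 5% of the time throughout. Repeat runs with different starting means agreed to within about two percentage points.

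**Step 3: a second set of assumptions.** With a shift of 0.5 SD, continuous data and 15 pairs, rank-sum against signed-rank power is 20% against 32% at r = 0.3, 18% against 42% at 0.5, and 14% against 62% at 0.7. At r = 0 the two tests agree (24% each). At r = −0.3 the rank-sum test is too liberal, rejecting 7.7% under no change, but a negative correlation is not what one expects for repeat scores in the same patient.

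**Step 4: a worked example.** Take 15 baseline scores 1, 2, 2, 3, 3, 3, 4, 4, 4, 5, 5, 5, 6, 6, 7. Ten participants gain one level and five do not change, so later scores are 2, 3, 2, 4, 4, 3, 5, 5, 5, 6, 5, 6, 7, 6, 7.

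- Rank-sum: U = 87, expected 15 × 15/2 = 112.5, SD √(15 × 15 × 31/12) = 24.1. z = 25.5/24.1 = 1.06, p = 0.29.
- Signed-rank: ten non-zero differences, all positive, each with rank 5.5. Sum = 55, expected 27.5, SD √(10 × 5.5²/4) = 8.70. z = 27.5/8.70 = 3.16, p = 0.0016.

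Nobody worsened and two thirds improved, yet the named test reports no evidence of change.

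**The case against.** The strongest reply is that this is a slip of the pen with little consequence. The same sentence asks for a paired *t*-test, and McNemar's test is chosen for within-group categorical data, so the authors plainly regard the data as paired. The stated hypotheses compare active with sham. The rank-sum fallback for that comparison is correct, and the repeated measures ANCOVA does not use it. The trial is a feasibility study without an efficacy power calculation, and the outputs it lists (recruitment, adherence, adverse events, variability, potential effect size) do not need a within-group p-value.

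Most of this stands and limits the severity. It does not make the named test right: the article states a specific test, so this is not a detail left to the SAP, and a program written from the sentence would carry the error over.

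A reader might infer three stronger things that the article does not support.

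- *That every within-group p-value will be wrong.* The paired *t*-test remains first choice, categorical outcomes go to McNemar's test, and several secondary outcomes (VDS out of 100, K-MASA out of 200, tongue and lip pressure in kPa) are not coarse scales and may not need the fallback.
- *That the error could create a false signal of benefit.* With positive correlation the test rejects too rarely.
- *That the trial will claim an effect because change is significant in one arm and not the other.* The article makes no such claim.

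**Conclusion.** The point holds: the rank-sum test is the wrong fallback for the paired comparison, and nothing elsewhere in the article corrects it. The harm is confined to within-group tests for which normality is judged to fail, and there it lies in missed change.

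The size depends mainly on the correlation. Under the assumed SD and gain, the power lost is about 11 percentage points at correlation 0.3 (49 − 38), 26 at 0.5 (62 − 36), 45 at 0.7 (80 − 35) and 59 at 0.8 (92 − 33). None of these inputs is in the article, so the figures illustrate the effect and do not predict it. Estimates of change and variability do not depend on which test is used. Severity is minor to moderate.

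**What to change.** In the within-group sentence of the Statistical analysis section, replace the rank-sum test with the Wilcoxon signed-rank test. Leave the rank-sum test in the between-group sentence. If an SAP or analysis program has been written from this text, check that it names the signed-rank test for the paired comparisons.

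The cost is one term. Design, sample size and data collection do not change. Labelling the within-group tests as descriptive would be a reasonable addition, but it is optional and not needed to correct this error.

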### Randomization

Participants will be randomized using a block randomization method stratified by stroke chronicity (subacute vs. chronic) and age (19–64 vs. ≥65 years). Allocation will be concealed in opaque envelopes; a blinded investigator will assign participants (1:1) without involvement in outcome assessments.

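### Both between-group analyses of FOIS and PAS omit the randomisation factors, and neither is named as primary

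*Protocol article*

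**What the plan says.** The Randomization section describes 1:1 block randomisation "stratified by stroke chronicity (subacute vs. chronic) and age" (19–64 against 65 and over), which gives four strata. The Discussion, describing the same trial, lists centre as a third stratification factor.

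FOIS and PAS are primary outcomes at baseline and post-intervention only. Their course over all four assessments is listed under Secondary outcomes.

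The Statistical analysis section gives two between-group methods for such measures:

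- "Between-group changes at each time point will be assessed by a two-sample" t-test, or by a Wilcoxon rank-sum test where normality is not met. No covariate is mentioned.
- A repeated-measures ANCOVA that "will assess group differences across time points, using baseline as a covariate". Baseline is the only covariate named.

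The section does not say which of these is primary for FOIS or PAS. A randomisation factor appears once, as a subgroup: "subgroup analyses will be conducted by age (19–64 and 65" and over. Chronicity does not appear in the section.

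Under Sample size estimates, the article says that "a formal power calculation for efficacy was not performed". It lists the variability and potential effect size of the primary and secondary measures among the trial's products.

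**The concern.** Stratified randomisation makes the arms more alike on the stratifying factors. If those factors predict outcome, the group difference varies less from trial to trial than it would under simple randomisation. An analysis without them does not see this: it leaves their contribution in the residual variance, so its standard error describes a less well balanced trial than the one run. The result is an interval that is too wide and a test that rejects too seldom under the null.

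Two further features add to this. The change-score test subtracts the baseline with a fixed coefficient of 1 instead of estimating the coefficient, which costs precision unless the correlation is near 1. And for the same post-intervention data the section allows a t-test, a rank-sum test or an ANCOVA result. The first two are separated by a normality check on a 7-level and an 8-level ordinal scale with 15 per arm.

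At stake is the usefulness of the between-group estimate. The trial is to inform the sizing of a larger one, and the Discussion hypothesises significant improvement over sham. With 30 participants, an interval wider than the design warrants, from an analysis that was not fixed beforehand, serves neither purpose well.

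**Working it through.** **Inputs from the article.** 30 participants, 15 per arm; two binary stratification factors (Randomization section). The article derives no power or precision figure, so there is nothing to reproduce; 30 rests on practicality and on a precedent of 28.

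**Assumed inputs.** Raw-score SD 1 in each arm; two-sided 5% level; true difference 0.8 SD where power is shown; blocks of 4; strata equally common; baseline-to-post correlation r; strata explaining a share R² of variance. Normal theory is used, so for ordinal scales the results are approximate.

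**Step 1: change score against baseline ANCOVA.** The per-person variance is 2(1−r) for change and 1−r² for ANCOVA. The ratio is (1−r²)/(2(1−r)) = (1+r)/2, and the ratio of interval widths is its square root.

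| r | Variance ratio | Width ratio | Power, change | Power, ANCOVA |
|---|---|---|---|---|
| 0.3 | 0.65 | 0.81 | 43% | 60% |
| 0.5 | 0.75 | 0.87 | 56% | 68% |
| 0.7 | 0.85 | 0.92 | 78% | 84% |
| 0.9 | 0.95 | 0.97 | 99.7% | 99.8% |

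**Step 2: strata omitted, closed form.** With 15 per arm, the unadjusted standard error is about √(2/15) = 0.365. With perfect balance on the strata, the true sampling SD is about √(2(1−R²)/15). At R² = 0.25 this is √(1.5/15) = 0.316. Simulation, which allows for incomplete blocks, gives a mean standard error of 0.365 against a true SD of about 0.32, and a type I error of about 3%.

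**Step 3: strata added to a baseline ANCOVA.** Simulation with r = 0.7 and 8,000 trials per setting; R² is the share of residual variance that the two factors explain.

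| R² | Type I, strata omitted | Type I, strata included | Mean CI width, omitted → included | Power, omitted → included |
|---|---|---|---|---|
| 0% | 0.056 | 0.054 | 1.08 → 1.09 | 83% → 82% |
| 10% | 0.040 | 0.050 | 1.09 → 1.04 | 83% → 85% |
| 20% | 0.032 | 0.054 | 1.09 → 0.98 | 85% → 90% |
| 30% | 0.021 | 0.046 | 1.09 → 0.91 | 86% → 93% |

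A repeat run extended to R² = 40% gave type I error of about 0.016 with the strata omitted and 0.047 with them included. The unadjusted change-score test is conservative to a similar degree (0.041, 0.034 and 0.024 at 10%, 20% and 30%). At R² = 0 the unrounded power is 82.9% against 82.3%, so adjusting for factors that predict nothing costs 0.6 points. In the repeat run, the mean estimate was 0.80 for all three analyses when the true difference was 0.8, so omitting the strata causes no bias.

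**Step 4: centre.** If centre is also a stratum, there are 2 × 2 × 4 = 16 possible cells, or 30/16 ≈ 1.9 participants per cell. Adjusting for every cell is not workable.

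**The case against.** The strongest case against runs as follows. This is a feasibility trial without a power calculation, so there is no power target to fall short of. The error is in the conservative direction. Nothing in the article shows that age or chronicity predicts FOIS or PAS: the Discussion calls them more relevant than stroke etiology as predictors of response to stimulation, which is not a statement about outcome variance. The two analyses may not compete at all: the two-sample test would serve the baseline-to-post endpoint and the ANCOVA the four-visit secondary outcome. And covariates are often left to an analysis plan, which is not shown.

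Most of this stands, and it limits the point. The gain depends on correlations and stratum effects that the article does not give, and it could be nil. The division of roles between the two analyses is plausible, but the article does not state it. Deferral to an analysis plan is a weaker reply, because the section does fix the tests, the switching rule, the covariate and the subgroup; what it fixes leaves out the randomisation factors.

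A reader might infer more than the article supports:

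- That the unadjusted test is the declared primary analysis. It fits the primary endpoint best, but no analysis is so named, and the ANCOVA is adjusted for baseline.
- That the effect size and SD handed to the next trial would be wrong. Under stratified 1:1 allocation the mean difference stays unbiased and the outcome SD is unaffected; only the standard error of the difference is overstated.
- That leaving out a chronicity subgroup is an error. It is a choice, and interaction tests with 15 per arm would be very imprecise.

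**Conclusion.** The point holds as a matter of precision and of clarity about the primary analysis. It is not one of bias or of a missed power target. The article stratifies on chronicity and age group and then states two between-group analyses, neither of which carries those factors and neither of which is named as primary for FOIS and PAS.

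If the factors explain 10% to 40% of variance, type I error falls to about 4% to 2%, and intervals are wider than the design warrants. The change-score test loses further precision against baseline ANCOVA, whose variance is 25% lower at r = 0.5 and 15% lower at r = 0.7. This second loss does not apply to the planned ANCOVA. All of these sizes rest on assumed correlations, stratum effects, equal strata and blocks of 4. The remedy is nearly free, so it is worth making even though the benefit cannot be fixed from the article.

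**What to change.** In the Statistical analysis section:

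1. Name one primary analysis for FOIS and for PAS at post-intervention: ANCOVA of the post-intervention score on arm, baseline score, chronicity and age group, reported with a 95% confidence interval.
2. Add chronicity and age group to the repeated-measures model across visits.
3. Replace the normality-based switch with a rank analysis stratified by the randomisation factors, set in advance as the sensitivity analysis. This also covers the ordinal nature of both scales.
4. Reconcile the Randomization section with the Discussion on whether centre is a stratification factor. If it is, enter the factors as main effects and do not adjust for up to 16 cells.

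The cost is wording and two degrees of freedom (residual 27 to 25 against the baseline ANCOVA). Centre with four sites would take three more (25 to 22). If chronicity and age group are not prognostic, adjusting for them loses under 1 point of power. Both are already recorded for randomisation, so no new data are needed.

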## Introduction and rationale

It has been reported that around 78% of acute stroke patients are prone to develop dysphagia as a consequence of stroke, which is the malfunction of the capacity to swallow (1). Dysphagia severity is related to the stroke location and lesion volume, and additional factors like brain atrophy, white matter changes can further compromise swallowing recovery. Although dysphagia may improve spontaneously with time, approximately 11.5 percent of the patients will develop a long-term disability (2), leading to high mortality and morbidity rate due to several medical complications related to pneumonia, malnutrition, dehydration and recurrent aspiration (1, 3). Therefore, prompt treatment is critical for these patients.

Non-invasive stimulation, particularly transcranial direct current stimulation (tDCS) has drawn attention for post-stroke dysphagia, due to its potential to aid swallowing recovery in addition to its easy application, and low-cost (4) and safety. tDCS uses a constant low-intensity direct current to regulate neuronal activity in the cerebral cortex by positioning electrodes on the scalp (2). Applying a direct current to a specific area of the scalp can modify the threshold of neuronal resting potential and influence the firing of neurons (3). While administering tDCS, the combined effect of the polarity of the electrode (anode or cathode), the intensity and duration of the application can potentially induce depolarization or hyperpolarization of the targeted neurons' membrane (3, 4).

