### General health

A general health examination will be performed during the four mentioned periods. The examination will be composed of a combination of various tests, which include nutritional examination (blood sample recollection of albumin and protein) (56), evaluation of the presence of low skeletal muscle index (56, 57), and immunologic tests (number and type of infections, white blood cell count and antibiotic use history) (58).

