### Vital signs and physical examination

The vital signs will be assessed after 5 min of resting in a seated position by measuring systolic and diastolic blood pressure, pulse and body temperature. They will be assessed at Baseline, Mid-intervention and post-intervention.

The physical examination will be performed at Baseline, Mid-intervention, Post-intervention, and Follow-up. It includes assessing height, weight, skeletal muscle index, body mass index, body water, protein, minerals, and body fat percentage.

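### The only rule that names the physical examination reduces continuous body measures to three clinical categories, so moderate change by arm in weight, BMI and body water would not be visible

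*Protocol article*

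**What the plan says.** The section Vital signs and physical examination gives the timing: "The physical examination will be performed at Baseline, Mid-intervention, Post-intervention, and Follow-up". It then gives the content: "It includes assessing height, weight, skeletal muscle index, body mass index, body water, protein, minerals, and body fat percentage". Every item named is a number on a continuous scale.

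The Statistical analysis section opens with a general rule: "The study outcomes will be presented as mean, standard deviation (SD), median, minimum, and maximum for continuous data". Within-group change, between-group tests and a repeated-measures ANCOVA with baseline as covariate follow. In its second paragraph, on categorical variables, it gives a separate rule for this examination: "In the case of physical examination, the results at each time point will be categorized as Normal, Abnormal Not Clinically Significant, and Abnormal Clinically Significant". The only summary stated for these categories is their frequencies.

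Three other places bear on the point:

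- The Introduction attributes mortality and morbidity in long-term dysphagia to "several medical complications related to pneumonia, malnutrition, dehydration and recurrent aspiration".
- General health, among the secondary outcomes, includes a "nutritional examination (blood sample recollection of albumin and protein") and "evaluation of the presence of low skeletal muscle index".
- Safety and adverse event monitoring has all adverse events coded in MedDRA and reported by group. Its examples of dysphagia-related events are pneumonia, enteritis, fever and abnormal breath sounds. The list is open and does not name malnutrition, dehydration or weight loss.

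**The concern.** A three-level clinical rating suits a qualitative body-system examination. Here the listed content is body composition, and no qualitative item is named for the rating to apply to. A frequency table by visit shows how many patients fall in each category. It does not show how far anyone moved. A patient who loses weight or body water without changing category looks the same before and after.

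Safety is one of the trial's two stated aims. Weight and body water are the measures in the article that bear most directly on the malnutrition and dehydration it mentions. If one arm drifted moderately in either, the stated tables could look alike in both arms although the data to show the drift had been collected at four visits.

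**Working it through.** **1. Reading the sections together.** No figure in the article is in dispute, so the first step is textual. For each measure, the question is which stated rule would show change by arm.

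| Measure | Rule naming the physical examination | Other stated route |
|---|---|---|
| Weight, BMI, body water, minerals, body fat | Three categories, frequencies | None specific; only if recorded as an adverse event |
| Skeletal muscle index | Three categories, frequencies | General health, but as presence or absence of a low value |
| Protein (body composition) | Three categories, frequencies | General health covers protein from blood, a different quantity |
| Albumin | Not part of this examination | General health, under the general rule for continuous outcomes |

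The gap is therefore mainly weight, BMI and body water. The General health route also has a loose end. The text says four periods, but Table 1 marks the combined general health and quality-of-life row at V2, V13 and V25, not at V24 (a laboratory test is marked at V24).

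**2. How much categorising can cost.** The article gives n = 15 per arm. It gives no SD, effect size, alpha or definition of abnormal. Assumed here: two-sided alpha 0.05, normal data, a difference of d SD in change, one abnormal threshold on that same scale, and an abnormal share p0 in the unaffected arm of 5%, 10% or 20%.

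*Continuous analysis* (two-sample t-test): noncentrality = d × √(n/2), with 28 degrees of freedom and critical value 2.048. For d = 0.8: 0.8 × √7.5 = 2.19, power 0.56.

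*Abnormal yes/no*: the abnormal share in the affected arm is p1 = Φ(Φ⁻¹(p0) + d). Power is the exact probability that Fisher's test gives p ≤ 0.05 with 15 per arm. For d = 0.8 and p0 = 0.05: p1 = Φ(−1.645 + 0.8) = 0.199, power 0.08.

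| d (SD) | Continuous | p0 = 5% | p0 = 10% | p0 = 20% |
|---|---|---|---|---|
| 0.5 | 0.26 | 0.02 | 0.05 | 0.08 |
| 0.8 | 0.56 | 0.08 | 0.17 | 0.22 |
| 1.0 | 0.75 | 0.19 | 0.30 | 0.37 |

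Counts at this size are also coarse. With 0 of 15 abnormal in one arm, 4 of 15 in the other gives Fisher p = 0.100, and it takes 5 of 15 to reach p = 0.042.

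**3. Sensitivity to the definition of abnormal.** Assume BMI 23 (SD 3), height 1.65 m (SD 0.08) and one arm losing D kg more than the other, with SD of change S kg. Neither cut below is in the article.

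| D, S (kg) | Weight change, t-test | Abnormal = loss above 5% of baseline weight | Abnormal = BMI outside 18.5–25 |
|---|---|---|---|
| 2, 2 | about 0.75 | about 0.21 | about 0.02 |
| 2, 3 | about 0.42 | about 0.13 | about 0.02 |
| 3, 2 | about 0.98 | about 0.62 | about 0.02 |
| 3, 3 | about 0.75 | about 0.33 | about 0.02 |

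The last column is an artefact of a two-sided band. With BMI SD held at 3, the share outside it at baseline is Φ(−1.5) + [1 − Φ(0.667)] = 0.067 + 0.252 = 0.319. A 2 kg loss lowers mean BMI by 2/1.65² = 0.73, and the share outside falls to 0.286, because loss also moves heavier patients into the normal range.

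**The case against.** The strongest reply is that the article never says the categories replace numeric summaries. The general rule for continuous data comes first, the three-category sentence stands among the categorical methods, and Table 1 calls the row physical and medical examination. The sentence may have been meant for the clinician's overall finding, and the content list opens with the word *includes*. A fuller analysis plan, not shown here, could add weight by visit. This stands to the extent that the article does not exclude such tables. It does not remove the point: the general rule speaks of study outcomes, the physical examination sits outside the outcome sections, and the one rule that names it is categorical.

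A reader might infer that malnutrition or dehydration could occur in one arm and go unreported. The documents do not support that. Clinically significant abnormalities are counted at each visit, recorded adverse events are reported by group from an open list, and albumin, protein and low skeletal muscle index are separate outcomes. Nor does the Introduction rank malnutrition and dehydration as the main harms; it lists them beside pneumonia and recurrent aspiration.

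It is also fair to say that power is an imperfect yardstick. The article disclaims a formal power calculation for efficacy and names no test in the sentence on physical examination. The calculations show loss of information, not a failed test. A reader might also argue that the pilot loses variance estimates for the later trial. The Sample size section promises those for primary and secondary outcomes, and weight and body water are not among them.

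**Conclusion.** The point holds as a minor one. The only analysis rule that names the physical examination puts largely continuous measures into three categories at each visit. Followed as written, it would hide moderate within-category change by arm, mainly in weight, BMI and body water.

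The loss cannot be fixed at one figure because the article does not define abnormal. With a single threshold, power for a 0.8 SD difference is 0.56 as continuous against 0.08 to 0.22 as yes/no. Cutting at a 5% loss gives a smaller but still material gap. The near-total loss under a two-sided BMI band should not be quoted as the effect of this plan. All these figures rest on assumed values and on two categories, whereas the plan has three. They also do not model a clinician who judges each result against earlier visits, which the article neither requires nor rules out.

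**What to change.** In Statistical analysis, limit the three-category rule to qualitative examination findings, or keep it as a supplement. For the continuous measures listed under Vital signs and physical examination (at least weight, BMI, body water and skeletal muscle index), state that the value and the change from baseline will be reported by arm at each visit as mean, SD, median and range. Add the baseline-adjusted active-minus-sham difference with its confidence interval, labelled as descriptive safety information.

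The cost is one or two sentences and a few tables. The data are already scheduled, so no new measurements, visits or staff are needed, and no clinical rule changes.
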